### **4.9 Treatment response**

Treatment response will be operationalised as scores of “very much improved” (1) or “much improved” (2) on the Clinical Global Impression – Improvement scale (CGI-I) administered at 3FU [9]. We will also report numbers needed to treat, with 95% confidence intervals, based on the proportions of responders in each group at 3FU.

### **4.10 Naturalistic long-term follow-up analyses (objective #2)**

All trial participants will be naturalistically followed up (i.e., participants will be able to seek other kinds of help after the primary endpoint at 3FU) and assessed at 6FU and 12FU. As previously described, the blind assessors will remain blind for the individual participants’ treatment allocations until data for the final 12FU assessment have been collected. The naturalistic long-term follow-up analyses will be carried out in stage 2 (corresponding to objective #2). The analyses will be performed on the second locked database and will be published in paper 2.

The stage 2 analyses will be carried out using linear quantile mixed models and logistic regression, which are described for stage 1. In addition, we will perform complementary linear mixed models (estimating a difference in means) for each of the linear quantile mixed models performed. The linear mixed models will be performed to enable comparisons with previous trials in the field.

Primarily, the stage 2 regression models will include the 3FU, 6FU, and 12FU assessment points, and will evaluate in a within-group analysis whether the potential treatment effects demonstrated for BIP TIC at 3FU in stage 1 are sustained at 12FU.

Additionally, we will also enter all available assessment points to a separate regression model to investigate whether there are significant between-group effects at 12FU. Results from such between-group analyses, however, will be interpreted with caution, given the risk of bias associated with long follow-up periods (e.g., patients with poor short-term outcomes are more prone to receive other potentially effective treatments during the follow-up period) [10].

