## Appendix

### 4.7 Primary outcome analysis (objective #1)

The primary outcome is tic severity, as measured by the YGTSS-TTSS, at the primary endpoint (3FU). The primary outcome analysis (objective #1) will be based on all available data up to this time point and conducted according to the intention-to-treat (ITT) principle.

As the YGTSS-TTSS is a composite measure resulting in an integer-valued variable ranging from 0 to 50, statistical modelling will focus on the median of the outcome (i.e., the 0.5-quantile) rather than its mean. Specifically, all the randomised participants will be included to estimate a linear quantile mixed model [6-8], taking into account individual differences in pre-treatment symptomatic status and treatment response. The model will include fixed effects for time (the YGTSS-TTSS at baseline, post-treatment, and 3-month follow-up) and subject-specific effects as a random intercept factor to account for the variances between and within participants. Linear quantile mixed models use all available data, can account for correlation between repeated measurements on the same subject, can flexibly model time effects, and can handle missing data.

To enable comparisons with previous trials within the field, which traditionally have used regression models based on means rather than medians, we will also perform complementary analyses of the primary outcome measure at the primary endpoint using a linear mixed model (estimating a difference in means). Similar to the linear quantile mixed model, the linear mixed model will include fixed effects of time (the YGTSS-TTSS at baseline, post-treatment, and 3-month follow-up) and subject effects as a random intercept factor to account for the variances between and within participants. Like linear quantile mixed models, linear mixed-effects models use all available data, can account for correlation between repeated measurements on the same subject, can flexibly model time effects, and can handle missing data. Results from the linear mixed-effects model will be presented as a complementary analysis to the linear quantile mixed model.

The estimated treatment effect will be reported with the accompanying 95% confidence interval (CI) and *p*-value. The alpha level of 0.05 will be used as the threshold for statistical significance throughout all trial analyses.

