## **Appendix**

### **4.8 Analyses of secondary outcomes**

Secondary outcome measures (details shown in the full study protocol) will be analysed using similar statistical methods as the primary outcome, that is, with linear quantile mixed models, and complemented with linear mixed models to facilitate comparison with previous trials. Dichotomous variables will be analysed using logistic regression. The results will be presented as estimates or odds ratios, as appropriate, for the regression coefficients, with their respective 95% confidence intervals and *p*-values.

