### **5.2 Analyses**

The short-term health economic evaluation (objective #3) will compare BIP TIC and the comparator at the primary endpoint (3FU). These results will be published together with the efficacy results (objective #1) in paper 1. As a long-term evaluation, we will then perform the same analyses at the end of the follow-up period (12FU) using cumulative information collected throughout the follow-up. These results will be published together with the results of the naturalistic follow-up (objective #2) in paper 2.

The health economic evaluation will be performed from three different perspectives, with gradually increasing costs included for each perspective:

1. The first perspective is the health organisation payer perspective, which includes direct treatment costs, of BIP TIC and the comparator, for the clinic. This comprises personnel costs such as therapist time, administration time, IT platform maintenance, and other overheads.
2. The second perspective will additionally include other healthcare resource use outside the clinic for the children, such as costs for medical appointments (outside the trial) and medications.
3. The third perspective will further comprise other societal costs, including productivity losses for the children related to absenteeism and presenteeism from school and leisure activities, and productivity losses for the parents due to absenteeism from work.

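### The stage 2 logistic regression for CGI-I response names no within-child correlation, so read plainly it under-detects loss of response between 3FU and 12FU

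*Combined protocol and SAP*

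**What the plan says.** For score outcomes, SAP 4.7 specifies a mixed model with "subject-specific effects as a random intercept factor to account for the variances between and within participants". For binary outcomes, SAP 4.8 says only: "Dichotomous variables will be analysed using logistic regression". Protocol 8.1 is equally brief.

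SAP 4.9 defines treatment response as the two best grades on the "Improvement scale (CGI-I) administered at 3FU", and defines it at no other visit. Protocol Table 1 schedules CGI-I at post-treatment, 3, 6 and 12 months.

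SAP 4.10 then carries the stage 1 methods forward: "The stage 2 analyses will be carried out using linear quantile mixed models and logistic regression, which are described for stage 1". It adds: "Primarily, the stage 2 regression models will include the 3FU, 6FU, and 12FU assessment points". Their purpose is to "evaluate in a within-group analysis whether the potential treatment effects demonstrated for BIP TIC at 3FU in stage 1 are sustained at 12FU". No margin or other criterion for sustained is given. SAP 4.7 sets the only threshold: "The alpha level of 0.05 will be used as the threshold for statistical significance throughout all trial analyses".

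**The concern.** In stage 1, response is one value per child, and logistic regression without a subject term is valid. In stage 2 each child can contribute three ratings to the same model. A logistic model that treats those rows as independent handles the 12FU v 3FU comparison as if two separate groups of children had been rated. It is a paired comparison. With positive correlation between a child's ratings, the independence standard error is too large, so the test rejects too rarely and real loss of response is missed more often than it need be.

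Durability is a named secondary objective, and CGI-I response is the only dichotomous outcome that the SAP defines. Responder rate is also the outcome of the cost-effectiveness analysis, which SAP 5.2 repeats at 12FU. If the team takes a non-significant change to mean that response was sustained, the error works in favour of that conclusion.

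**Working it through.** **Plan's own figure.** There is none to reproduce. The 97% power in protocol 5.3 concerns the TTSS at 3FU and does not bear on this analysis.

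**Inputs.**
- n = 100 children in BIP TIC: the per-arm figure in protocol 5.3. Complete CGI-I at 3FU and 12FU is assumed.
- Alpha 0.05 (SAP 4.7), taken as two-sided.
- Random-intercept SD 2.95 and residual SD 2.04 (protocol 5.3).
- Response falling from p1 = 50% at 3FU to p2 = 35% at 12FU: assumed.
- Visit entered as a factor (assumed), so the contrast is the log odds ratio between the two visits.

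**Step 1, correlation.** CGI-I rates improvement against admission (protocol 5.5.3), so the nearest analogue is change in TTSS from baseline. Under a random-intercept model the intercept cancels in a change score. Two changes that share a baseline have variance 2 × 2.04² = 8.32 each and covariance 2.04² = 4.16, so their correlation is 0.50. Dichotomised at an even split, this becomes (2/π) × arcsin(0.50) = 0.33.

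For a range:
- An assumed latent correlation of 0.3 gives (2/π) × arcsin(0.3) = 0.19.
- The correlation of TTSS level is 2.95² / (2.95² + 2.04²) = 8.70 / 12.86 = 0.68, which gives (2/π) × arcsin(0.676) = 0.47 at an even split. At margins of 50% and 35% the same latent value gives 0.45.

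**Step 2, standard error.** Write q = 1 − p.
- Independence variance: 1/(n p1 q1) + 1/(n p2 q2) = 0.0400 + 0.0440 = 0.0840, so SE = 0.2898.
- Correct variance: 0.0840 − 2ρ / (n √(p1 q1 p2 q2)) = 0.0840 − 0.0839ρ.
- At ρ = 0.33: 0.0563, so SE = 0.2372.
- Ratio: 0.2898 / 0.2372 = 1.22.

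**Step 3, actual error when nothing changes.** With p1 = p2 the ratio is 1/√(1 − ρ) = 1/√0.67 = 1.22. The actual two-sided error is 2 × [1 − Φ(1.96 × 1.22)] = 1.7%.

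**Step 4, power.** The log odds ratio is ln(0.35/0.65) = −0.619.
- Independence model: Φ[(0.619 − 1.96 × 0.2898) / 0.2372] = Φ(0.216) = 59%.
- Correlation handled: Φ(0.619 / 0.2372 − 1.96) = Φ(0.650) = 74%.

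| Binary correlation | SE ratio | Power, independence | Power, correlation handled |
|---|---|---|---|
| 0.19 | 1.11 | 58% | 66% |
| 0.33 | 1.22 | 59% | 74% |
| 0.45 (0.47 at an even split) | 1.35 | 59% | 82% |

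**Step 5, cross-check with other assumptions.** For a fall from 45% to 35% with n = 110, the same formula gives 30% v 44% at ρ = 0.3 and 26% v 57% at ρ = 0.5. Simulating the unpaired test against McNemar's test (20,000 samples) gave 29% v 44% and 26% v 59%. At ρ = 0 the formula gives 33% for both methods, as it should.

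**The case against.** **The SAP is silent; it does not prescribe an independence model.** This is fair. The word ordinary does not appear, and the analysts may intend a mixed logistic model. Protocol 8.2 also speaks of a random intercept for each outcome measure. But that paragraph covers linear quantile and linear mixed models and supplies no model for a binary outcome. SAP 4.10 refers the reader back to a description that contains no subject term. The plain reading is the one examined here, and the remedy is to state the model.

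**Response is defined only at 3FU.** True, so a repeated binary outcome is an inference. It is a reasonable one: CGI-I is scheduled later, logistic regression is named for stage 2, and the 12FU economic analysis uses responder rate.

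**A reader might infer inflated false positives between arms.** The documents do not support this. Inflation needs one arm term pooled over visits. SAP 4.10 asks about the between-group effect at 12FU, and a visit-specific contrast is essentially unaffected.

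**A reader might take the TTSS correlation of 0.68 as the right input.** That figure is driven largely by stable differences in severity between children, which cancel in a rating of change. Children who respond differently to treatment could raise the CGI-I correlation above the 0.33 used here, but the documents give no figure.

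**The error need not favour durability.** This stands in part. If durability were judged by whether a confidence interval excludes a material loss, too large a standard error would make sustained harder to claim. The favourable direction holds only if non-significance is read as durability. The SAP does not state that rule, but it states no other.

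**Conclusion.** The point holds as a gap in specification with a predictable consequence. Followed as written, the stage 2 method gives too large a standard error for the within-group 12FU v 3FU contrast in CGI-I response. At a binary correlation of 0.33 the loss is about 15 percentage points of power for a fall from 50% to 35%. Over the range examined it is about 8 points (58% v 66%) to 23 points (59% v 82%). These sizes rest on assumed response rates, an assumed correlation and complete follow-up of 100 children. The direction needs only a positive within-child correlation.

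The consequence is limited to dichotomous secondary outcomes in a naturalistic secondary objective. One might infer that the durability claim as a whole is unsound, but TTSS durability is tested with a subject random intercept and is untouched. The missing criterion for sustained is a separate gap, which a correlation-aware model does not close.

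**What to change.** Before the second database lock, and preferably before stage 1 results are known:

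- In SAP 4.10, for repeated dichotomous outcomes, replace logistic regression with a named repeated-measures logistic model that has visit and arm-by-visit terms. It can be a logistic mixed model with a participant random intercept, or GEE clustered on participant with robust standard errors.
- Report the 12FU v 3FU contrast with its 95% confidence interval.
- Extend the CGI-I response definition in SAP 4.9 to 6FU and 12FU.
- Keep logistic regression as described in SAP 4.8 for single-visit analyses such as 3FU response.

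The cost is a few sentences of SAP text and a standard routine, with no new data or participants. Each option has a downside to state. GEE odds ratios are population-averaged, and unweighted GEE needs stronger missing-data assumptions, which matters over 12 months of naturalistic follow-up. Mixed-model odds ratios are subject-specific, so they will not match odds ratios computed from the raw response proportions.

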## **8.2 SECONDARY OBJECTIVE #1: 12-MONTH DURABILITY OF THE TREATMENT EFFECTS**

All trial participants will be naturalistically followed up and assessed 6 and 12 months after the end of the 10-week treatment. Linear quantile mixed-effects models will be implemented for the primary and secondary outcome measures. As in the primary objective, for each outcome measure, the model will include fixed effects of time (5 time points) and subject effects as a random intercept factor to account for the variances between and within participants. In addition, we will perform complementary linear mixed models (estimating a difference in means) for each of the linear quantile mixed models performed. The linear mixed models will be performed to enable comparisons with previous trials in the field.

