### 2 Study objectives

#### 2.1 Primary objective

Objective #1: To determine the clinical efficacy of internet-delivered behaviour therapy (hereby referred to as BIP TIC) for reducing tic severity (as measured by the Yale Global Tic Severity Scale - Total Tic Severity Score [YGTSS-TTSS]; *primary outcome measure* [1]) in children and adolescents with Tourette's Disorder and Persistent (Chronic) Motor or Vocal Tic Disorder [2], compared with an active control intervention (hereby referred to as *the comparator*). The *primary endpoint* is the 3-month follow-up after the end of treatment (3FU).

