## **Appendix**

### **2.2 Secondary objectives**

Objective #2: To establish the 12-month durability of the above-described treatment effects.

Objective #3: To conduct a health economic evaluation of BIP TIC, from multiple perspectives, both in the short term (primary endpoint) and the long term (12-month follow-up)..

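### SAP 4.10 leads objective #2 with a within-arm analysis of BIP TIC, although the effect whose durability is in question is defined against the comparator; the planned between-arm model should lead

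*Combined protocol and SAP*

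**What the plan says.** SAP 2.1 sets the primary objective as efficacy of BIP TIC relative to an active control, the comparator. SAP 2.2 then gives objective #2: "To establish the 12-month durability of the above-described treatment effects". Read together, the effect whose durability is at issue is a between-arm effect.

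SAP 4.10 plans two stage 2 analyses and ranks them.

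- **Lead:** "Primarily, the stage 2 regression models will include the 3FU, 6FU, and 12FU assessment points". These models "will evaluate in a within-group analysis whether the potential treatment effects demonstrated for BIP TIC at 3FU in stage 1 are sustained at 12FU".
- **Second:** "Additionally, we will also enter all available assessment points to a separate regression model to investigate whether there are significant between-group effects at 12FU". The SAP adds that these results call for caution, because patients who did poorly in the short term are likelier to obtain other effective treatment during follow-up.

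The same section says of both arms that "participants will be able to seek other kinds of help after the primary endpoint at 3FU". It gives no margin, interval rule or other criterion for *sustained*.

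Protocol 8.2 describes a five-time-point model for this objective and names no lead contrast. Protocol section 8 gives the SAP precedence. SAP 4.12 defines effect sizes only as between-group quantities, and the 12-month economic evaluation in SAP 5.2 compares the arms.

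**The concern.** A change from 3FU to 12FU within BIP TIC contains nothing about the comparator, so it cannot by itself show that a difference between the arms lasts. It can go wrong in two directions. If BIP TIC stays flat while the comparator catches up, the lead result looks like durability although no between-arm effect remains. If both arms worsen equally, it looks like loss although the effect is intact.

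The reason given for caution about the between-group result applies to the within-arm result as well. BIP TIC families may also take up other treatment after 3FU, and that can make gains look maintained. The natural fluctuation of tics noted in protocol 9.2 is likewise uncontrolled in a single arm, whereas randomisation balances it in expectation between arms.

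At stake is the headline of paper 2. Protocol section 13 makes national implementation depend partly on BIP TIC being durable.

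**Working it through.** **The plan's own figure.** The documents give no power or precision for objective #2. The only figure is in protocol 5.3: 97% power for a 3-point median difference at 3FU with 100 per arm, using a random-intercept SD of 2.95 and a residual SD of 2.04. A simple cross-sectional median comparison gives:

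- total SD = √(2.95² + 2.04²) = 3.587
- SE = 1.2533 × 3.587 × √(2/100) = 0.636, where 1.2533 = √(π/2) is the factor for a median under normality
- 3/0.636 = 4.72, so power is about 99.7%

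This does not reproduce 97%. The time coding in the plan's model is not stated, and the mismatch does not bear on this point.

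**What each contrast can tell apart.** Inputs were the two SDs above, 100 per arm, a 3-point difference at 3FU, two-sided 0.05 (sidedness assumed) and 20,000 simulated normal trials per scenario. The within-arm test is 12FU minus 3FU in BIP TIC, on means. 6FU is left out for simplicity.

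| Course after 3FU | True difference at 12FU | Within-arm change non-significant | Between-arm test at 12FU significant |
|---|---|---|---|
| Both arms flat | 3 | 94.9% | about 100% |
| BIP TIC flat, comparator improves 3 | 0 | 95.0% | 5.1% |
| Both worsen by 3 | 3 | 0% | about 100% |
| BIP TIC worsens 0.5, comparator improves 2.5 | 0 | 60% | 4.7% |
| BIP TIC worsens 3, comparator flat | 0 | 0% | 4.9% |

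Hand check: the within-arm SE is 2.04 × √(2/100) = 0.288. A 0.5-point change is then 1.73 SEs, and Φ(1.96 − 1.73) ≈ 0.59, which agrees with row 4. With 88 per arm (an assumed 20% missing from 110), rows 2 and 4 become 95.0% and 64%.

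The within-arm test cannot separate rows 1 and 2, and it flags loss in row 3 where the effect is intact. It detects the loss in row 5, where BIP TIC alone relapses.

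**Precision of the contrasts, median-based, 100 per arm.** The SD of an individual change is 2.04 × √2 = 2.885.

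- Within-arm change: 1.2533 × 2.885/√100 = 0.36
- Change in the between-arm difference, 3FU to 12FU: 1.2533 × 2.885 × √(2/100) = 0.51; 2/0.511 = 3.91, so about 97% power for 2 points
- Unadjusted 12FU difference: 0.64; 2/0.636 = 3.15, so about 88% power for 2 points

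These rest on the pilot's residual SD. With assumed change SDs of 5 and 6 and 99 per arm (220 × 0.9/2), the SE of the change in difference is 0.89 and 1.07, and power for 2 points is about 61% and 46%.

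For a 1.5-point loss at those same SDs, the within-arm test has about 66% and 51% power. The between-arm change contrast has about 39% and 29% for a shift of the same size.

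**The case against.** Four points can be made for the plan.

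- **The between-group analysis is there.** A reader of the lead sentence alone might infer that the randomised, blinded comparison is thrown away. It is not. The next paragraph of SAP 4.10 pre-specifies it with all visits, and assessors stay blind to 12FU. A comparator that caught up would show in the same paper. This stands, and it limits the fault to ranking.
- **Other treatment may be taken up unequally.** If comparator families obtain more of it, the between-arm difference shrinks for reasons unrelated to BIP TIC's own course. This is a fair reason to say what the 12FU difference means, namely the effect of allocation irrespective of later treatment. That is a choice of estimand. It does not turn a single-arm course into evidence about a difference.
- **No rule that p > 0.05 means *sustained* is written.** A reader might infer one, since 0.05 is the threshold throughout, but the SAP also reports estimates with 95% CIs. The documented gap is a missing criterion. The table treats non-significance as *sustained* only as an assumption.
- **The within-arm analysis is more precise.** Correct: at equal SDs its SE is smaller by a factor of √2. It would be tempting to say that the between-arm contrast is also the better powered one. The figures do not support that.

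Nor do protocol 8.2 and SAP 4.10 contradict each other on the model. The five TTSS assessments in protocol Table 1 are those of the SAP's second model, and 8.2 simply names no lead contrast.

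**Conclusion.** The concern holds as one of order and labelling. Objective #2 is about a between-arm effect; the analysis placed first does not use the comparator, and the one that does is placed second with a caution that applies to both. In the flat-BIP-TIC scenarios, the lead analysis gives the same answer about 95% of the time whether the effect is 3 points or zero. That follows from the contrast itself and does not depend on the SD. The other percentages rest on the pilot SDs, normal data and equal arms.

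The within-arm result remains a useful description of whether BIP TIC participants keep their scores, provided it is labelled that way. The primary analysis at 3FU, its alpha and the safety reporting are untouched. Should-fix, because the objective is secondary.

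**What to change.** In SAP 4.10, before unblinding:

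1. Make the planned all-randomised, all-visit model the primary analysis of objective #2, with arm, visit and arm-by-visit terms written out so that both contrasts below can be estimated.
2. Report the BIP TIC minus comparator TTSS difference at 12FU, and the change in that difference from 3FU to 12FU, each with a 95% CI. State that they estimate the effect of allocation irrespective of later treatment.
3. Keep the 3FU-to-12FU changes within each arm, with CIs, as supportive and descriptive. State that a non-significant change will not be read as *sustained*.
4. Word protocol 8.2 to match.

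No new data or visits are needed, and both models are already planned. The cost lies in the claim itself: the lead 12-month contrast is less precise than the within-arm one, and it may be less favourable or diluted by later treatment. The 61% and 46% power figures at the larger assumed SDs should be kept in view when a null result is interpreted.
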